## Abstract

**Background:**

Between 40 and 50% of patients with Parkinson’s disease (PD) experience anxiety and depression, associated with impaired physical function, high care dependency and mortality. Recently, the United States National Institutes of Health has urged the implementation of mindfulness practices in chronic illness care. Most research to date has examined the effects on chronically ill patients of complex interventions using a combination of mindfulness techniques. In PD patients, however, such complex modalities appear to hinder the technique mastery. Hence, the aim of this trial is to investigate the effects and underlying mechanism of individual mindfulness techniques among PD patients, as well as exploring participants’ experience in using individual mindfulness techniques as a lifestyle intervention for stress and symptom management.

**Methods:**

We will conduct an assessor-blind three-arm randomized waitlist-controlled trial with a descriptive qualitative evaluation. Up to 168 PD patients will be recruited from community settings and out-patient clinics, and randomized to meditation, yoga, or usual care group. Meditation and yoga sessions of 90-minute are held weekly for 8 weeks. Primary outcomes include anxiety and depression. Secondary outcomes include PD-related motor and non-motor symptoms and quality-of-life; and level of mindfulness and biomarkers of stress and inflammatory responses will be measured as mediating variables. All outcome evaluations will be assessed at baseline, 8 weeks, and 24 weeks. Following the intention-to-treat principle, generalized estimating equation models and path analysis will be used to identify the treatment effects and the mediating mechanisms. A subsample of 30 participants from each intervention group will be invited for qualitative interviews.

**Discussion:**

The study would also generate important insights to enhance the patients’ adaptation to debilitating disease. More specifically, symptom management and stress adaptation are highly prioritized healthcare agenda in managing PD. The research evidence will further inform the development of community-based, nurse-led compassionate care models for neurodegenerative conditions, which is complementary to existing health services.

**Trial registration:**

WHO Primary Registry – Chinese Clinical Trials Registry number: ChiCTR2100045939; registered on 2021/04/29 (https://www.chictr.org.cn/showproj.html?proj=125878).

## Background

Parkinson’s disease (PD) is the second most common neurodegenerative disease, affecting approximately 10 million people worldwide, and its estimated prevalence is expected to double by 2040 [1]. PD symptoms include four cardinal motor symptoms (resting tremor, rigidity, bradykinesia, and postural instability) and a range of non-motor symptoms including cognitive impairment, insomnia, constipation, and neuropsychiatric problems, which could severely limit patients’ daily function, independence, and HRQOL [2]. Adjusting to physical and psychosocial changes brought on by PD can be highly demanding and is associated with great psychological distress [3, 4]. Between 40 and 50% of PD patients experience anxiety and depression [5], and anxiety and anxious depression are the prominent psychopathological phenotype in PD [6]. Psycho-immunological studies of PD suggest that psychological distress and depressive symptoms are risk factors for psychiatric comorbidities and accelerated disease progression. Patients with high psychological distress reportedly experience greater disability, fast progression of physical symptoms, poor treatment compliance, increased comorbid conditions and mortality, high healthcare utilisation, and high caregiver distress [7].

While pharmacological intervention is used as the first-line treatment for more severe psychiatric manifestations in PD patients, its effects are suboptimal and even undesirable [8]. Mounting evidence suggests that psychological distress exerts a direct influence on PD pathogenesis by altering the hypothalamic-pituitary-adrenal (HPA) axis and potentiating inflammatory responses [9]. High cortisol levels provoked by HPA axis dysfunction and stress-induced upregulation of pro-inflammatory cytokines are associated with dopaminergic cell loss, increased symptom severity, and PD progression [10, 11]. These findings imply the potential benefits of psychological care not only for psychological outcomes and stress-related physiological parameters, but also for motor and non-motor symptoms of PD.

The United States National Institute of Health has urged the implementation of mindfulness practices in chronic illness care. Mindfulness, defined as ‘the awareness that emerges through paying attention on purpose, in the present moment, and nonjudgmentally to the unfolding of experience moment by moment’ [12], is a form of mental training that aims to improve an individual’s core psychological capacities, such as attentional and emotional self-regulation. Its positive effects on stress management have been demonstrated among populations with chronic conditions including psychiatric problems [13–15], cancer [16], chronic pain [17], and cardiovascular diseases [18]. A recent meta-analysis reported that mindfulness practices reduce physiological markers of stress, i.e., rebalancing the HPA axis with decreased cortisol levels, and improving inflammatory responses with reduced pro-inflammatory cytokines interleukin-6 (IL-6) and tumour necrosis factor-α (TNF-α) [19, 20]. Though conceptualisations of mindfulness vary, all highlight its role in enhancing attention and awareness of thought and emotion, and all contrast mindful information processing with automatic, habitual, or heuristic information processing [21]. The Liverpool Mindfulness Model elucidates the link between mindfulness and attention regulation processes on well-being [22]. The mindfulness training of attention skills underpins emotional and cognitive flexibility, bringing about the ability to maintain non-judgmental awareness of one’s own thoughts, feelings, and experiences which, in turn, will change the quality of one’s behaviour and lead to positive health outcomes and well-being [23].

With the popularity of mindfulness in wellness promotion, its research evidence on PD population remains relatively limited. Most mindfulness research examines the effects of the Mindfulness-Based Stress Reduction (MBSR) program conceptualised by Jon Kabat-Zinn. This group-based program focuses on progressive acquisition of mindfulness. An 8-week workshop is taught by certified trainers and entails weekly group meetings (2.5 h), a one-day retreat (7 h practice) between sessions 6 and 7, homework (45 min daily), and instruction in two core formal techniques: meditation and yoga postures [13–15]. Despite preliminary positive outcomes on emotional well-being having been reported in a few small-scale trials [24, 25], a 2017 systematic review concluded that the significant outcomes were contradicted and evidence to support MBSR practice for PD was inconclusive [26]. The inconclusive results may be related to the high dose and complex modalities (i.e., combined use of mindfulness techniques) of the MBSR program, aimed at enhancing participants’ extended immersive experience. A previous systematic review reported high dose (weekly ≥ 180 min) programs are associated with reduced adherence and increased physical intolerance caused by PD conditions [27], which may hinder PD patients’ skill mastery.

Indeed, mindfulness encompasses a family of practices, including meditation and yoga which are commonly used to promote well-being of patients with chronic illness [28]. Meditation is a form of relatively static mental training that starts with focused attention on an object to develop attentional stability and non-judgemental awareness of the current mental state [29]. This helps produce a deep state of relaxation, resulting in enhanced emotional and physical well-being. Yoga cultivates mindfulness experience through physical exertion [30]. The mental training starts with focused attention on various physical or emotional experiences arising from dynamic yoga movements. Apart from mental relaxation, the physical training of yoga may simultaneously target other major stressors in PD patients, including symptoms such as stiffness, muscle weakness and postural instability. However, the effects and acceptability of these individual mindfulness techniques remain underexplored in persons living with disabilities and chronic illnesses, such as PD.

To conclude, despite there being theoretical and empirical evidence suggesting the stress-relieving and health-enhancing effects of mindfulness interventions, a limited number of PD supportive interventions have focused on enhancing this attribute. Regarding the evolving stress-reducing effects of mindfulness, it is imperative to extend investigations into individual use of mindfulness practices, and to further examine their therapeutic value and underlying mediating mechanism, using both subjective and objective outcome measures, compared to usual care among persons with PD. This study aims to address these research gaps. The findings would provide a wider repertoire of evidence-based psychological interventions to support PD patients’ emotional health and symptom management.

### Aims and hypothesis

This study aims to:

examine the effects of individual mindfulness techniques – yoga and meditation – compared to usual care, on anxiety and depression, mindfulness, PD-related motor and non-motor symptoms, HRQOL and biomarkers of stress and inflammatory responses of PD patients over the 6-month study period;investigate whether biomarkers and level of mindfulness function as mediating variables in the effects that the mindfulness practices have on anxiety and depression, respectively; and.explore the experiences of PD patients in practising individual mindfulness techniques, and conditions that may influence their motivation, acceptability, and real-life practice.

The research hypotheses to be tested are:

PD patients who receive mindfulness interventions will report greater positive changes in anxiety and depression, mindfulness, PD-related motor and non-motor symptoms, HRQOL and biomarkers of stress and inflammatory responses on the completion of the intervention and at 4-month follow up, compared to the usual care group.The effects of mindfulness practices on anxiety and depression are meditated by a reduced level of physiological markers of stress and improved level of mindfulness demonstrated at post-test assessment.

The exploratory research question is:

3.What are the participants’ experiences in using yoga and meditation as lifestyle intervention for psychological distress management, particularly the perceived effects, how and why mindfulness works or does not work, and conditions which may influence their motivation, acceptability, and real-life practice?

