#### Secondary outcomes

*Movement Disorder Society-Unified Parkinson’s Disease Rating Scale (MDS-UPDRS, Chinese)* will be used to measure PD-related motor and non-motor symptoms [43]. MDS-UPDRS consists of four parts, which examine: (i) non-motor experiences (cognitive impairment, hallucinations, depressed mood, anxious mood, apathy, and dopamine dysregulation), (ii) motor experiences of daily living, (iii) examination of motor symptoms (tremor, rigidity, bradykinesia, gait and postural instability), and (iv) motor complications (dyskinesia and motor fluctuations), respectively. Higher scores indicate greater disease severity. Cronbach’s alphas are 0.79–0.93 [44].

*Chinese Five-Facet Mindfulness Questionnaire (Short-form)* will be used to measure perceived mindfulness [45]. Using a 5-point Likert scale, this 20-item scale assess five mindfulness domains: observing, describing, acting with awareness, non-judgment of inner experience, and non-reaction to inner experience. Cronbach’s α is 0.82 [46].

*Parkinson’s Disease Questionnaire-8 (PDQ-8, Chinese)* will be used to measure PD-related HRQOL [47]. The 8-item scale yields a summary index score capturing disease-specific HRQOL regarding mobility, activities of daily living, emotional wellbeing, social support, communication, cognition, body discomfort and stigma. Higher scores indicate worse HRQOL. Cronbach’s α is 0.80 [48].

Plasma cortisol, IL-6 and TNF-α will be collected. To control for variations of cortisol levels over the circadian rhythm, all blood samples will be collected at 14:00 to 16:00, as cortisol level in this sub-period is relatively stable and highly correlated with mean 24-h cortisol level [49, 50].

The expectation on treatment credibility refers to the respondent’s expectation of the stress-reducing effect of the received intervention. A 4-item questionnaire will be used, rating: (i) reasonableness of treatment, (ii) opinion of the therapist, (iii) expectation for improvement, and (iv) likelihood to recommend the treatment to others, on a 10-point scale (higher scores indicating higher expectation) [51].

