### Data analysis

Descriptive statistics will be used to summarize the socio-demographic characteristics and clinical data (as listed above) of all subjects at all time points. Generalized estimating equations (GEE) with unstructured working covariance matrix at the individual level with repeated measurements will be performed to compare all outcomes [1–5] between groups (i.e., time effect, group effect, group*time effect). An intention-to-treat principle will be adopted. Multiple imputations will be used to account for missing data, and reporting will follow the guideline published in *BMJ* [54]. Sensitivity analysis will be performed to compare the results between complete and non-complete cases. All demographic and clinical variables (e.g. age, gender, religiosity, expectation on treatment credibility, etc.) will be accounted for in the analysis. Both crude and adjusted GEE model analyses will be performed. All statistical tests will be two-tailed and statistical significance will be set at 0.025. IBM SPSS 25.0 will be used.

Path analysis will be used to examine the mediating role of biomarkers and level of mindfulness on the effect of mindfulness training on psychological distress. Based on the hypothesized mediation model (Fig. 2), a baseline path model will be first built, then a path model with the same structure for T1 will be added and linked by intra-correlations among the same variables. The mediation effects of biomarkers and level of mindfulness on the effect of mindfulness training on psychological distress will be assessed through the significance of the corresponding products of indirect path coefficients from mindfulness training to psychological distress, respectively [55]. In view of the possibility of violation of normality assumption, a bootstrapping approach, instead of the conventional multivariate delta method, will be used to estimate the standard errors and the confidence intervals of the product terms (mediation effects) [56]. The path analyses and the bootstrapping will be performed using IBM SPSS 25.0.

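### Every secondary outcome sits inside the tested hypothesis and is judged at the primary's 0.025 level, with nothing limiting formal claims to anxiety and depression

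*Protocol article*

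**What the plan says.** All references are to the protocol article.

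- **Aims and hypothesis.** The first research hypothesis to be tested reads "PD patients who receive mindfulness interventions will report greater positive changes in anxiety and depression, mindfulness, PD-related motor and non-motor symptoms, HRQOL and biomarkers", to be shown "on the completion of the intervention and at 4-month follow up, compared to the usual care group". The second covers mediation of the effect on anxiety and depression. Only the qualitative question that follows is set apart, introduced by "The exploratory research question is".
- **Abstract and Outcome measures.** "Primary outcomes include anxiety and depression"; motor and non-motor symptoms, quality of life, mindfulness and the biomarkers appear under secondary outcomes. The Abstract also calls mindfulness and the biomarkers mediating variables. On scoring, "MDS-UPDRS consists of four parts", with no statement whether a total or the parts are analysed. "Plasma cortisol, IL-6 and TNF-α will be collected".
- **Sample size estimation.** The level of 2.5% is a Bonferroni adjustment, given in the paragraph that takes psychological distress as the primary outcome. The items it divides between are not named.
- **Data analysis.** GEE models compare all outcomes through time, group and group-by-time effects. "All statistical tests will be two-tailed and statistical significance will be set at 0.025". The mediation effects "will be assessed through the significance of the corresponding products of indirect path coefficients".

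**The concern.** A level obtained by dividing 0.05 by two, in a paragraph about the primary outcome, becomes the significance rule for every secondary outcome and every indirect effect. Division by two cannot cover six to nine secondary scores in two active arms at two follow-ups.

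Unadjusted secondary tests do little harm when they are declared supportive. Here they belong to the hypothesis under test, and only the qualitative question is called exploratory. A single significant cytokine, or one MDS-UPDRS part at one visit, could therefore be reported as bearing out the first hypothesis. The text contains nothing to prevent that if the HADS comparisons were negative.

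**Working it through.** **Step 1: the plan's level.** 0.05 / 2 = 0.025, which reproduces the stated 2.5%. Two-sided, the critical value is 2.2414. The chance of a false result in the favourable direction is 0.0125 per test.

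**Step 2: number of secondary tests.** From Secondary outcomes: mindfulness, PDQ-8, cortisol, IL-6 and TNF-α make 5 scores. MDS-UPDRS adds 1 (total) or 4 (parts), giving 6 or 9. Treatment credibility is not counted as an efficacy outcome.

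- Full set of contrasts, each active arm against usual care at T1 and T2: 6 × 2 × 2 = 24, or 9 × 2 × 2 = 36.
- One group-by-time test per outcome: 6 or 9.

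Expected false positives at 0.025 are 0.15 (6 tests), 0.225 (9), 0.6 (24) and 0.9 (36).

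**Step 3: chance of at least one false positive, all secondary nulls true.** Under independence:

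- either direction: 1 − 0.975^k
- benefit only: 1 − 0.9875^k

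Under a common correlation ρ, write each statistic as √ρ·U + √(1−ρ)·e, with U shared and e independent standard normals, and average over U. For either direction, the probability of no rejection is the mean of [Φ((c − √ρ·U)/√(1−ρ)) − Φ((−c − √ρ·U)/√(1−ρ))]^k with c = 2.2414. For benefit only, drop the second term.

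| Tests (k) | Error counted | Independent | ρ = 0.3 | ρ = 0.5 | ρ = 0.7 |
|---|---|---|---|---|---|
| 36 | either direction | 59.8% | 47% | 34% | 22% |
| 36 | benefit only | 36.4% | 24% | 17% | 11% |
| 24 | either direction | 45.5% | 37% | 28% | 18% |
| 24 | benefit only | 26.1% | 19% | 14% | 9% |
| 9 | either direction | 20.4% | 18% | 15% | 11% |
| 9 | benefit only | 10.7% | 9% | 8% | 6% |
| 6 | either direction | 14.1% | 13% | 11% | 9% |
| 6 | benefit only | 7.3% | 6.5% | 5.6% | 4.5% |

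A joint group-by-time test has no single direction, so the benefit rows for 6 and 9 tests count half of each test's error as benefit.

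**Step 4: a structured correlation as a cross-check.** Assume 0.5 between arms (shared control), 0.5-0.7 between times and 0-0.5 between outcomes. Simulation gives 32-41% either direction and 16-23% benefit for 24 tests, and 40-55% and 21-32% for 36 tests. All lie inside the ranges above.

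**Step 5: indirect effects.** Four mediators (mindfulness and three biomarkers) and two distress outcomes give 8 products. If the mediators respond to treatment but do not affect distress, and the tests are independent, the chance of at least one false indirect effect is 1 − 0.975^8 = 18.3%. Correlation among the tests would lower this, as would mediators that do not respond.

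Both crude and adjusted GEE models are planned. The second look that this allows is not counted.

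**The case against.** Four objections carry weight.

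- **A correction exists.** The 0.025 is itself a Bonferroni level, and applying it to all tests holds the secondaries to a stricter standard than 0.05. This stands, so a reader should not infer that the plan has no correction. The level simply does not cover the secondary family.
- **A ranking exists.** The outcomes are labelled primary and secondary, and the trial is sized on psychological distress. This also stands: the text does not support saying that there is no hierarchy at all. But no rule uses the labels.
- **The count is a construction.** The article does not say that the four MDS-UPDRS parts are tested separately, and its group-by-time effect can be read as one joint test per outcome. The 6-9 test reading is therefore shown beside the 24-36 test reading. Error exceeds 2.5% on both.
- **This is ordinary content for an analysis plan.** Testing order among secondaries often sits there, and unadjusted secondaries are common. That would answer silence. Here the article states a rule for all tests and a hypothesis that spans all outcomes, so an analysis plan limiting formal claims to HADS would depart from the published text.

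The article does not use the word confirmatory for the first hypothesis. That status is inferred from its place among the hypotheses to be tested, set against the one question called exploratory. Nor does the article say that one significant secondary would establish the hypothesis. The concern is that nothing prevents such a claim.

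**Conclusion.** The point holds in a measured form. The stated rule leaves error across the secondary family uncontrolled, and the primary and secondary labels have no consequence for what may be claimed. With all secondary nulls true, at least one significant result in either direction has a chance of about 18-60% (24-36 tests) or 9-20% (6-9 tests). A false benefit has a chance of about 9-36% or 5-11%. The ranges run from a common correlation of 0.7 to independence. They rest on the assumed number of MDS-UPDRS scores, the assumed contrasts and the assumed correlations.

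A reader might infer that a false claim of benefit is more likely than not. The figures do not support this: only results in either direction pass 50%, and only towards the 36-test, weakly correlated end. A result favouring usual care would not support a hypothesis of greater improvement, and the benefit-only chance stays below 50% in every scenario. The 18% for indirect effects is a conditional upper figure and adds little to the case. The error rate of the primary family is a separate matter, not judged here.

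**What to change.** Two wording changes.

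1. In Data analysis, state that the 0.025 rule supports formal claims only for the HADS primary comparisons. State that the MDS-UPDRS scores, mindfulness, PDQ-8, cortisol, IL-6, TNF-α and the indirect effects are reported as supportive estimates with confidence intervals.
2. In Aims and hypothesis, limit the formally tested hypothesis to anxiety and depression, and list the other outcomes and the mediation question as secondary.

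If the team wants a formal secondary claim, it could test secondaries only in an arm whose primary comparison is significant, using Holm within that arm. This is optional and not needed to resolve the point.

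The cost is text only: no extra participants, data or analyses. The small downside is that an isolated secondary result can no longer be claimed as a confirmed effect.

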## Methods

### Study design and setting

This is a multi-centre, assessor-blinded, 3-arm randomised waitlist-controlled trial with sequential mixed-method design to evaluate the effect and acceptability of 8-week programs using individual mindfulness techniques (yoga alone and meditation alone), compared to wait-list usual care control. Figure 1 shows the CONSORT flow diagram. Repeated outcome measures will be assessed at three time points across the 6-month study period to quantitatively evaluate the immediate and sustained effects of each mindfulness technique on anxiety and depression and other physio-psycho-spiritual outcomes in PD patients, compared with the usual care control group. Assessment time points are: baseline (Prior to randomization, T_0_), 8 weeks (T_1_: 1-week post-intervention), and 24 weeks (T_2_: 4-month post-intervention).

